## Abstract

**Background:**

Anterior shoulder dislocation is a common injury and may have considerable impact on shoulder-related quality of life (QoL). If not warranted for initial stabilising surgery, patients are mostly left with little to no post-traumatic rehabilitation. This may be due to lack of evidence-based exercise programmes. In similar, high-impact injuries (e.g. anterior cruciate ligament tears in the knee) neuromuscular exercise has shown large success in improving physical function and QoL. Thus, the objective of this trial is to compare a nonoperative neuromuscular exercise shoulder programme with standard care in patients with traumatic anterior shoulder dislocations (TASD).

**Methods/design:**

Randomised, assessor-blinded, controlled, multicentre trial. Eighty patients with a TASD will be recruited from three orthopaedic departments in Denmark. Patients with primary or recurrent anterior shoulder dislocations due to at least one traumatic event will be randomised to 12 weeks of either a standardised, individualised or physiotherapist-supervised neuromuscular shoulder exercise programme or standard care (self-managed shoulder exercise programme). Patients will be stratified according to injury status (primary or recurrent). Primary outcome will be change from baseline to 12 weeks in the patient-reported QoL outcome questionnaire, the Western Ontario Shoulder Instability Index (WOSI).

**Discussion:**

This trial will be the first study to compare the efficacy and safety of two different nonoperative exercise treatment strategies for patients with TASD. Moreover, this is also the first study to investigate nonoperative treatment effects in patients with recurrent shoulder dislocations. Lastly, this study will add knowledge to the shared decision-making process of treatment strategies for clinical practice.

**Trial registration:**

ClinicalTrials.gov, identifier: NCT02371928. Registered on 9 February 2015 at the National Institutes of Health Clinical Trials Protocol Registration System.

**Electronic supplementary material:**

The online version of this article (doi:10.1186/s13063-017-1830-x) contains supplementary material, which is available to authorized users.

## Background

Traumatic anterior shoulder dislocation (TASD) is a common injury [1], especially within the second and third decades of life in young, active individuals [2], with a yearly incidence rate in the general population reported to be from 11.2 to 26.2 per 100,000 persons [3–7]. Following a first-time TASD, the risk for recurrent dislocations is high due to pathophysiological changes in the shoulder joint [8] with mean risk rates estimated to vary between 39% and 67% [4, 9, 10]. Recurrent dislocations may be serious with shoulder function being further compromised by every dislocation. Hence, patients are frequently limited in sports-related and social activities affecting quality of life (QoL) [11–14].

Treatment-wise, systematic reviews advocate for initial stabilising surgery in young, highly athletic, active, male patients with a primary TASD [1, 15] in spite of the expressed concern that early surgery exposes patients to unnecessary surgery-related complications and adds to societal treatment costs [16]. For other TASD patients (e.g. those aged 25–40 years, nonprofessional athletes, primary or recurrent dislocations) the evidence for optimal treatment (operative as well as nonoperative) is limited [1, 17]. Traditionally, post-traumatic standard care consists of closed reduction, followed by immobilisation in a shoulder sling and, if provided, some kind of physiotherapy [18]. Currently, there is no evidence-based exercise programme to prescribe for patients with TASDs [8] and the quantity and quality of studies investigating nonoperative treatment for this patient group is low [19]. Three randomised controlled trials (RCTs) investigating the effect of nonoperative (shoulder rehabilitation) versus operative treatment (arthroscopic or open Bankart procedures in addition to shoulder rehabilitation) in patients with primary TASD show that early operative reconstruction of the anterior capsulolabral complex is superior to nonoperative treatment in reducing redislocation rates [20–22]. However, the shoulder rehabilitation programmes used in these RCTs are poorly described making it difficult to reproduce, and they consist mostly of postoperative exercise principles. Thus, the nonoperatively treated patients may have been undertreated with specialised, intensive, nonoperative exercise regimes lacking [23]. Also, varying methodological issues exist that are expected to bias the findings of the RCTs [19, 23].

In other body regions, neuromuscular exercise has shown great potential in reducing joint pain, besides improving functional capacities and QoL [24–27]; e.g. neuromuscular exercise has shown to be as equally effective as early surgical reconstruction in patients with traumatic anterior cruciate ligament injuries in the knee, which is comparable with TASD on injury mechanism (traumatic origin, high impact), age (late teens to mid-30s), post-traumatic symptoms (pain, instability, loss of mechanical stability), besides reduction in physical and social function [24]. Hence, neuromuscular exercise also seems evident for patients with TASD due to loss of mechanical stability [28], and potentially impaired proprioceptive functions [29–31]. To our knowledge, such neuromuscular exercise programmes for increasing sensorimotor control and compensatory functional stability [25] have not yet been developed and tested scientifically on the shoulder [32].

In conclusion, the evidence for optimal treatment of patients with TASD (primary and recurrent) is lacking, and previous exercise programmes are poorly described and do not include the newest physiological knowledge for improving joint instability deficits. Sufficiently powered, good-quality and well-reported RCTs are needed to investigate nonoperative rehabilitation strategies in patients with TASD [33].

### Study objectives

The aim of this randomised controlled clinical trial is to evaluate the efficacy and safety of a 12-week, structured ‘Shoulder Instability Neuromuscular Exercise’ (SINEX) programme versus 12 weeks of a self-managed, training-based, shoulder exercise programme (‘standard care’), measured on the Western Ontario Shoulder Instability Index (WOSI) questionnaire [34] in patients with TASD (primary and recurrent). It is hypothesised that patients receiving 12 weeks of SINEX training will show superior improvement in short- and long-term shoulder-related QoL and function.

## Methods/design

### Study design

This trial is a multicentre research project in cooperation with three orthopaedic shoulder units in The Region of Southern and Northern Denmark. The study is a randomised (1:1), assessor-blinded, controlled trial with a parallel-group design investigating the efficacy and safety of a ‘SINEX training programme’ versus standard care for patients with TASD (primary and recurrent) with a primary endpoint after 12 weeks (3 months). The primary endpoint of 12 weeks was chosen since the primary effect measure is a patient-reported shoulder-related QoL outcome and not, as in previous trials, whether the shoulder dislocates or not. Thus, if there is no significant short-term effects of the SINEX programme, it is highly unlikely that there will be any long-term effects. Furthermore, long-term follow-up will be performed for all patients between 1 and 2 years from baseline. The protocol conforms to the recommendations from the EQUATOR network [35], using the Standard Protocol Items: Recommendations for Interventional Trials (SPIRIT) Checklist and Consolidated Standards of Reporting Trials (CONSORT) guidelines for RCTs [36, 37] Additional file 1.

### Settings and locations

Patients are recruited from shoulder outpatient clinics of orthopaedic departments in the Region of Northern Denmark (Aalborg University Hospital, Farsoe) and Southern Denmark (South-West Jutland Hospital, Esbjerg and Odense University Hospital, Odense).

### Participants

Participants included are classified as dynamic shoulder instability types (class B2) according to Gerber et al. [38], referring to patients with unidirectional shoulder instability initiated by trauma. Both men and women with primary or recurrent anterior shoulder dislocations are included, provided that they fulfil the following criteria:

#### Inclusion criteria

Age between 18 and 39 yearsMinimum one radiographically verified anterior shoulder dislocation (total dissociation of the humeral head relative to the glenoid)Self-reported shoulder trouble (physical and/or emotional), meaning diminished ability to participate or perform shoulder movements needed in sports/leisure activity and/or work tasks within the latest week

#### Exclusion criteria (any of the following)

Humeral fracture and/or bony Bankart lesion (visible on conventional radiographs at the time of presentation) warranted for surgery as decided by the orthopaedic surgeonPending surgery to the affected shoulder jointMore than five anterior shoulder dislocations (verified by patient record or subjective evaluation)Suspected competing diagnosis (e.g. rheumatoid arthritis, cancer, neurological disorders, fibromyalgia, psychiatric diseases)Sensory and motor deficits in the neck and/or shoulderPregnancyInadequacy in written and spoken DanishNot willing or able to attend 12 weeks of supervised SINEX therapy

### Procedure

Patients consulting emergency departments with a TASD will be treated according to standard procedures consisting of shoulder reduction followed by sling immobilisation in internal rotation and use of analgesics, if needed. After completion of the subacute phase (3–6 weeks) patients will attend one of the participating shoulder units for a routine check of the actual shoulder function. Potential candidates are then identified and screened for initial eligibility by an orthopaedic surgeon according to inclusion criteria 1–2 and exclusion criteria 1–5. Patients fulfilling the eligibility criteria are referred to the principal investigator (first author), who performs the final eligibility assessment according to inclusion criterion 3 and exclusion criteria 5–8. All patients are provided with written and verbal information about the study objectives, and a signed consent is obtained for those eligible and willing to participate. Patients not included or declining to participate will be asked to fill out the WOSI questionnaire, and report age and gender so as to improve the selection bias analysis.

### Randomisation and concealment of allocation

Patients are randomly assigned to either of the two groups. An independent biostatistician, with no involvement in the clinical care of the patients, prepares a computer-generated list of random numbers (1:1), which is subsequently packed at each trial site into sequentially numbered, opaque, concealed envelopes, stating which group each individual is allocated to. Patients are stratified based on injury status: (1) primary (first time) or (2) recurrent (second to fifth) dislocations.

At each recruitment site, envelopes are stored in a closed room and managed by a single research assistant. After randomisation the same research assistant forwards group assignments to the treating physiotherapist who contacts the patient for an appointment of the first exercise instruction. Patients are reassessed after 3 months (12 weeks of exercise) and again after 12 (52 weeks) and 24 months (104 weeks). A flowchart of participants and randomisation is presented in Fig. 1.

**Fig. 1 Fig1:**
[figure not shown]
Flowchart of the Shoulder Instability Neuromuscular Exercise (SINEX) study

### Blinding

The primary investigator and one research assistant, performing outcome measurements, are blinded according to treatment allocation and not involved in the treatment of patients. Though, blinding of treatment allocation for patient and physiotherapist is not possible. Patients involved are thoroughly informed (written and orally) that the optimal choice of treatment is truly unknown, thereby keeping the study hypothesis secret [36]. Further, to retain the blinding of the outcome assessors, patients are encouraged not to reveal their treatment assignment. Finally, all of the statistical analyses will be performed blinded according to group allocation and results will be interpreted in an author consensus statement prior to disclosing/revealing group allocation.

### Interventions

Both groups receive 12 weeks of active exercise treatment, information on correct ergonomic postures and instructions in active range of motion exercises and/or stretching of shoulder muscles if needed. Patients are asked not to seek other treatment for their current shoulder problem during the intervention period. After the end of intervention patients will be advised to continue their exercises and allowed to seek other treatment options. Patients experiencing additional dislocations or worsening of shoulder symptoms during the intervention period will be referred to an orthopaedic surgeon for a clinical evaluation of whether they can continue in the study. Withdrawn patients, due to either worsening of symptoms, surgery and/or retraction of participation consent, will be asked to complete all follow-up measurements to ensure a full dataset. Finally, patients are asked to fill out an exercise diary in relation to their home-based exercises.

### Control group

Participants allocated to standard care will begin their 12 weeks of self-managed training-based shoulder exercise programme with one introductory supervised physiotherapy session. Standard care consists of active exercises for the rotator cuff and scapular muscles as follows: strengthening exercises for the rotator cuff muscles (shoulder internal and external rotation with the subject’s elbow flexed to 90° and the elbow positioned at the subject’s side in addition to shoulder abduction performed inthe scapular plane. Mobility/co-activation of the scapular and core stability muscles is performed through the weight-bearing, four-point kneeling exercise, with simultaneous lift-off of one arm and the opposite leg. Patients are asked to perform the exercises three times weekly with 10 × 2 repetitions for each exercise. Participants are initially provided with a leaflet containing photos and descriptions of each exercise, besides general information about their current shoulder injury, potential future implications, and how to avoid pain and instability provoking shoulder movements. Finally, participants receive one phone call from a physiotherapist after 6 weeks of training to ensure progression and compliance with the exercises, in addition to having any patient-initiated communication that the patient may want to have regarding further shoulder-related questions. Patients allocated to standard care will be regarded as having completed the intervention with a minimum of two thirds (66%) of the planned home training.

### Intervention group

Participants allocated to the SINEX programme receive 12 weeks of individually physiotherapist-supervised exercise specifically, targeting the glenohumeral and scapular muscles. Moreover, functional kinetic chain exercises are incorporated for progressing to more difficult levels, mimicking daily activities and improving the transferability of everyday activities.

The SINEX programme is individually tailored within a standardised framework consisting of seven exercises (1–7): scapular setting and control (1), glenohumeral setting and control during internal (2) and external (3) rotation, co-contraction of glenohumeral muscles (4), dynamic glenohumeral stability (5), besides training of glenohumeral proprioception (6, 7).

Each exercise includes seven levels (A to G) of difficulty, ranging from a basic to an elite level. Exercises at the basic level (A to E) are performed with low load, large body support and focus on local shoulder muscle activity (quality before quantity). Exercises at the elite level (F to G) are performed with high load, less body support and increasing movement speed, according to the individual capability of each patient. The load and repetitions of each exercise are performed as follows; exercises 1–4 are performed according to the principle of strength training, meaning that basic and elite levels refer to low- and high-load training equal to 2 × 20–25 and 2 × 8–12 of 1 repetition maximum, respectively. Exercise 5 (dynamic shoulder stability) is performed with the use of time intervals equal to 3 × 10 and 3 × 20 seconds at basic and elite levels, respectively. For exercises 6 and 7 (proprioceptive training) the basic and elite levels are performed with 2 × 5 and 2 × 10 repetitions, respectively. Participants are instructed to perform each exercise at home as follows; exercises at basic levels (A to E) 7 days a week and exercises at elite levels (F to G) three times a week.

Participants are provided with online access to instructions and video recordings of each exercise and the accompanying levels of progression through the physiotherapy site www.digifys.com.

Participants are encouraged to progress exercises themselves, where relevant, with physiotherapists then evaluating the performance quality of each exercise at the supervised sessions. Hence, supervised sessions are provided throughout the 12 weeks, lasting approximately 45 min each. Supervised sessions are given twice a week for the first 2 weeks and then once a week for the remaining 10 weeks. Physiotherapists decide the amount of supervision, based upon movement control and capabilities of the individual patient. Participants allocated to SINEX are considered to have satisfactory completion of the supervised sessions with attendance of at least seven supervised sessions (out of 14 possible sessions) equal to 50% attendance. Furthermore, to be considered compliant with the intervention participants must have completed at least two thirds (66%) of the planned home-based exercises. For quality assurance, physiotherapists are instructed, and continuously encouraged, to attend at least seven supervised sessions within the 12-week intervention period. A full description of the exercise programme, including structure, content, progression guidelines and overall concept is provided in Additional file 2.

### Physiotherapists

To be involved as a physiotherapist, attendance at two training sessions on how to administer the individualised supervision of patients according to the two intervention protocols is required. Furthermore, all physiotherapists are initially provided with a ‘pilot’ patient to practice the individualised supervised sessions and must have completed at least 2 weeks of supervised sessions before starting up study participants. Physiotherapists are allowed to contact the primary investigator regarding any exercise-based challenges that they may have, though, without revealing treatment allocation of the individual participants.

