### Data collection and follow-up

Two outcome assessors (primary investigator and one research assistant) perform all baseline and follow-up assessments. Before and during data collection outcome assessors train together the test procedures of objective outcomes to unify performance and interpretation. Also, thoroughly described test protocols for the objective outcome measurements are prepared.

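### One of the two blinded outcome assessors is also the physiotherapists' contact for exercise problems, so a patient-specific question can disclose SINEX allocation before the examiner-conducted 12-week tests

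*Protocol article*

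**What the plan says.** Three sections of the protocol article describe the same person.

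- **Blinding:** "The primary investigator and one research assistant, performing outcome measurements, are blinded according to treatment allocation and not involved in the treatment of patients".
- **Data collection and follow-up:** "Two outcome assessors (primary investigator and one research assistant) perform all baseline and follow-up assessments".
- **Physiotherapists:** "Physiotherapists are allowed to contact the primary investigator regarding any exercise-based challenges that they may have", with the qualification "though, without revealing treatment allocation of the individual participants".

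The Blinding section adds a second safeguard, on the patient's side: "to retain the blinding of the outcome assessors, patients are encouraged not to reveal their treatment assignment".

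The arms differ in how much a physiotherapist does. Under Control group, standard care has "one introductory supervised physiotherapy session", a telephone call at 6 weeks, and any contact the patient starts. Under Intervention group, SINEX has seven exercises, each with levels A to G, progressed individually at supervised sessions over the 12 weeks.

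**The concern.** Advising treating physiotherapists on exercise delivery sits badly with the statement that the assessors "are blinded according to treatment allocation and not involved in the treatment of patients". The rule against disclosing allocation stops a physiotherapist from naming the arm. It does not stop the content of a question from showing it, and it depends on each physiotherapist's discretion. If the investigator learns that a particular patient is in SINEX and later examines that patient, the 12-week test is no longer blinded. Because SINEX generates far more supervised contact, such disclosures would fall mainly on that arm.

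At stake are the tests an examiner conducts at 12 weeks, listed in Table 1 and under Key secondary outcomes: the apprehension, relocation and surprise tests (scored yes/no), the objective part of the Constant-Murley score, isometric strength and proprioception. The first two are the most exposed, because they depend most on the examiner. The Discussion acknowledges that patients and physiotherapists cannot be blinded, so the trial's assessor-blinded label rests on these two assessors.

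**Working it through.** The protocol gives no figure for unblinding, so there is none to reproduce. Three things can be checked.

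**1. Which arm would questions concern?**
- SINEX supervised sessions (Intervention group): 2 per week × 2 weeks + 1 per week × 10 weeks = 14. This matches the 14 possible sessions that the section states.
- Standard care planned contacts (Control group): 1 session + 1 call = 2.
- Ratio: 14 / 2 = 7 to 1.

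This compares opportunities for a question to arise. It is not a rate of unblinding. Patient-initiated contact in standard care would lower it by an unknown amount.

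**2. How many patients could a question be about?**
- Inputs (Timeline, trial status and publication plan): recruitment from March 2015, with 50 patients included by October 2016, taken as 19.5 months.
- Treatment period: 12 weeks = 84 days; 84 / 30.44 = 2.76 months.
- Sites (Settings and locations): 3.
- Accrual: 50 / 19.5 = 2.56 patients per month.
- In treatment at once: 2.56 × 2.76 = 7.1 patients.
- Per site: 7.1 / 3 = 2.4 patients.
- Range for 19 to 20 months: 50 / 19 × 2.76 = 7.3, and 50 / 20 × 2.76 = 6.9, so 2.3 to 2.4 per site.

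Both arms must be counted. A blinded assessor who knows only that a site's question concerns SINEX does not know which of that site's patients are in SINEX. With two or three patients in treatment, however, one detail such as sex, side or number of dislocations may be enough. The Procedure section has the principal investigator make the final eligibility assessment. If that is the same person, as I read it, this investigator has already met the participants.

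**3. What must happen for a test to be unblinded?**
- The question points to a recognisable patient.
- Its content is specific to SINEX: an exercise level, a proprioceptive exercise, or progression at a supervised session.
- The primary investigator, not the research assistant, then does that patient's 12-week tests.

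All three are needed. The article does not say how assessments are divided between the two assessors, so the exposed share cannot be calculated.

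**The case against.** The protocol foresaw the risk and answers it in the same sentence that allows the contact. A general question about teaching or progressing an exercise unblinds nobody. The caller's identity need not show the arm either, since "attendance at two training sessions on how to administer the individualised supervision of patients according to the two intervention protocols is required". Both programmes train rotation and the scapular muscles, and the 6-week call in standard care also deals with progression, so some questions would fit either arm. Blinding has support as well: the assessors train together and follow written test protocols, strength is read from a dynamometer, and open-chain repositioning is read from a laser on a target scale. The primary outcome is completed by the patient.

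All of this stands, and it limits the point. What it leaves open is the patient-specific question whose content belongs only to SINEX.

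A reader might go further in three ways, and the document supports none of them:

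- That the safeguard cannot work. It does cover general questions and those that identify no patient.
- That a question points to the one SINEX patient at a site. Half of 7.1 over three sites is 1.2, but that count assumes the assessor already knows who is in SINEX.
- That assessor blinding is the only protection for these outcomes. Joint training and written test protocols also help, although they do not replace blinding.

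**Conclusion.** The point holds as a limited design weakness. The primary investigator's advisory role is in tension with the claim of no involvement in treatment, and the safeguard leaves a gap for patient-specific questions. The gap falls mainly on SINEX: 14 planned contacts against 2. The pool in which a patient might be recognised is small, about 7 in treatment overall and 2.4 per site, if accrual is even over time and sites; the document confirms neither.

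Neither a frequency of unblinding nor a size of bias can be stated. Any bias would affect the examiner-conducted secondary outcomes at 12 weeks, most plausibly the yes/no instability tests and the objective Constant-Murley component. For strength and repositioning the instrument limits examiner judgement, though encouragement could still affect effort. A reader might infer that the trial's main result is compromised. It is not by this route: the WOSI is self-reported, by patients who know their treatment in any case.

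**What to change.** Amend the Physiotherapists section as follows.

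- Questions about an individual patient's exercises go to an existing team member who does no outcome assessment. If a research assistant is named, confirm that this is not the assessing assistant; the article does not say whether the assistants who handle the envelopes are different people.
- If such a question nevertheless reaches the primary investigator, the other assessor does that patient's 12-week tests and is told nothing of the reason.
- General questions about the programmes may continue as now.

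In addition, each assessor records a guess of allocation, patient by patient, straight after the 12-week tests, so that the success of blinding can be reported.

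The cost is a one-paragraph amendment and one extra item on the assessment form. No new staff are needed, provided a suitable non-assessor is already on the team; the arrangement with the other assessor needs none in any case. Physiotherapists lose direct access to the primary investigator for patient-specific questions, and scheduling of the two assessors becomes slightly less flexible. With 50 of the planned 80 patients included when the article was submitted, the change could still have protected later participants.
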